#### Primary data

The paper questionnaires will be scanned using the Electric Paper TeleForm software, in which they are subjected to detailed plausibility tests. The primary data will be analysed using descriptive statistics, tests for mean differences in independent samples and multivariable multilevel analyses to combine GP practice-level data from the online survey with individual patient survey data. All individual interviews will be audio-recorded and then transcribed and pseudonymised. The transcripts will be analysed with the structuring qualitative content analysis according to Kuckartz [49] using the software MAXQDA Analytics Pro. First, main categories will be developed a priori on the basis of the interview guideline, and then inductive subcategories will be developed during the coding process. The coding process will be carried out independently by two researchers with a subsequent consensus-finding procedure.

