#### Summative evaluation: primary data

The primary data for the summative evaluation will be collected by two standardised cross-sectional patient surveys in the intervention group pre and post implementation. Patients who visited the GP practice before implementation of the intervention act as a pre-implementation baseline. After implementation, a second patient survey will be conducted in the same GP practices (post implementation). The summative evaluation using primary data addresses the following research question:

Do patients in GP practices post-implementation report better vaccine literacy than patients pre-implementation?

Vaccine literacy is defined as a secondary outcome, as an association with vaccination uptake is known from the literature [29, 30].

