#### Primary data

##### Pre-post patient survey

The patient survey will be conducted in n = 50 randomly selected intervention GP practices that will be drawn from the population of n = 1057 GPs of the intervention group, stratified by ASHIP. The selected practices will receive the study materials for the two patient surveys pre and post implementation. The recruitment of patients will be done by the practice staff. Patients will be asked to complete an anonymous, paper-based questionnaire after their consultation with the GP. The questionnaires will be handed out in sealed envelopes and can be completed in the GP practice or at home. For the pre-implementation survey, patients who visited the GP practice in the 4–8 weeks before the intervention starts will be recruited. For the post-implementation survey, patients who visit the GP practice in the end of the intervention will be recruited. Each of the GP practices participating in the patient survey is asked to recruit a minimum of n = 25 patients for each survey round (2x n = 1250 patients). To increase the response, the practices receive a material incentive in the form of a gift box after n = 10 questionnaires and for all further questionnaires a financial incentive of 5 € per questionnaire.

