#### Primary data collection

In the pre-post patient survey, the secondary outcome vaccine literacy and further constructs such as general health literacy, psychological antecedents of vaccination behaviour, intention to get vaccinated, knowledge about vaccination, as well as numerous confounders and sociodemographic information will be assessed. The outcome vaccine literacy is assessed using the validated subscale of the Health Literacy Population Survey Project 2019–2021 (HLS19) instrument (HLS19-VAC-DE) [40]. General health literacy is measured with the generic short version of the instrument for measuring health literacy in the general population (HLS19-Q12; [40]. Psychological antecedents of vaccination behaviour are surveyed with the short version of the associated validated 5 C scale [18, 41]. The intention to get vaccinated is surveyed in a vaccine-specific manner using the item from the study by Betsch et al. [42].

Knowledge about influenza and pneumococci vaccination is assessed using an instrument based on the validated scale developed by Zingg & Siegrist [43]. (Un)met information needs regarding vaccination are assessed with items based on an instrument developed by Neumann et al. [44]. In addition to the listed central constructs, possible moderators such as the GPs’ empathy (Consultation and Relational Empathy scale) [45, 46] and trust in the GPs and medical assistants [47] are also included in the questionnaire. Furthermore, patient experiences regarding communication with the practice staff are surveyed. These include aspects such as carrying out a vaccination check, reminding, answering questions regarding vaccinations, and distributing written information. Sociodemographic variables (e.g., age, gender, employment) will be collected at both time points (pre and post implementation), as this is an anonymous survey with independent patient populations.

The focus of the online survey of GPs and medical assistants is on their experiences with and evaluation of the intervention. These aspects will be assessed with both self-developed instruments and validated instruments. For assessing the self-reported communication competence, the validated scale Medical Communication Competence Scale [48] is used. Furthermore, the online survey will include questions on structural characteristics of the GP practices such as size and type of the practice as well as sociodemographic characteristics of the GPs and the medical assistants (e.g., age, gender).

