***Summative evaluation (secondary and primary data)***			
**Secondary data**: Extract of pseudonymised contract GP billing data according to § 295 SGB V, n = 2114 GPs (n = 1057 GPs each in the intervention and control group) and at full utilisation ≥ 147,980 patients	**Primary outcome**: Influenza vaccination rate **Secondary outcome**: Vaccination uptake rate of the vaccinations recommended by the STIKO for patients aged 60 and older (except for influenza)	-	Descriptive statistics, pre-post comparison (intervention/control group), cluster analysis, subgroup analyses
**Primary data**: Cross-sectional patient survey in intervention practices (n = 50), pre- and post-implementation (2 x n = 1250 patients), paper & pencil survey	**Secondary outcome**: Vaccine literacy	**Further secondary outcome**: HLS19-VAC-DE subscale of the HLS19 instrument (40)	Descriptive statistics, multivariable regression models, multilevel analysis

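### The text plans independent-samples mean tests for the patient survey while Table 1 lists multilevel analysis for vaccine literacy; the plan should say which answers the pre-post question, because both waves come from the same 50 practices

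*Protocol article*

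**What the plan says.** The article gives vaccine literacy formal status: "Vaccine literacy is defined as a secondary outcome" (Summative evaluation: primary data). The same section asks whether patients report better vaccine literacy after implementation than before.

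The sampling design is clear:
- "The patient survey will be conducted in n = 50 randomly selected intervention GP practices" (Pre-post patient survey).
- "a second patient survey will be conducted in the same GP practices (post implementation" (Summative evaluation: primary data).
- Each practice "is asked to recruit a minimum of n = 25 patients for each survey round (2x n = 1250 patients" (Pre-post patient survey).
- The patients are not linked between waves: "this is an anonymous survey with independent patient populations" (Primary data collection).

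The analysis is described in three places:
- Data analysis, Primary data, lists descriptive statistics and then "tests for mean differences in independent samples and multivariable multilevel analyses to combine GP practice-level data from the online survey", with the sentence going on to the individual patient data.
- The abstract names mean comparisons and multilevel analyses side by side for the survey data.
- The vaccine-literacy row of Table 1 reads "Descriptive statistics, multivariable regression models, multilevel analysis". It has no mean test and no linkage condition.

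**The concern.** The pre-post comparison of vaccine literacy is the natural use of a two-sample mean test in this survey. Such a test treats the 2 × 1250 questionnaires as unrelated observations. They are unrelated as persons, but not by practice: patients of one practice share their doctor, staff and catchment area, and the same practices supply both waves.

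The text states a purpose for the multilevel analysis, namely bringing practice-level data from the online survey together with patient data. It does not mention a comparison of waves. For the secondary data, the same Data analysis section says that clustering is taken into account. It attaches no such condition to the survey mean tests.

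The p-value and standard error for a named secondary outcome are at stake. With two different methods named and neither designated, the choice could also be made after both results are known.

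**Working it through.** **Inputs from the article.** K = 50 practices, m = 25 patients per practice per wave (the requested minimum), and the same practices in both waves with different patients. The stated survey size reproduces: 50 × 25 = 1250 per wave. The article gives no power calculation, ICC or effect size for vaccine literacy, so there is no further figure of its own to reproduce.

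**Assumptions.**
- ICC: 0.08 is the article's figure for vaccination uptake (Sample section). None is given for literacy, so 0.02 is shown beside it.
- CAC, the correlation of a practice's effect between the two waves: not given. The range 0.5 to 1.0 is shown.
- Two-sided 5% level: stated for the secondary data and assumed here for the survey.

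**Formula.** Write σ² for the total variance of one patient's score.
- Variance of one wave mean: σ²/(Km) × [1 + (m − 1)·ICC].
- Covariance of the two wave means through shared practices: σ²·ICC·CAC/K.
- Variance of the difference: 2σ²/(Km) × [1 + (m − 1)·ICC − m·ICC·CAC].
- Variance that the independent-samples test uses: 2σ²/(Km), a standard error of √(2/1250) = 0.04 SD.

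The variance ratio is therefore VR = 1 + 24·ICC − 25·ICC·CAC. The true type I error of a nominal 5% test is 2 × [1 − Φ(1.96/√VR)].

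| ICC | CAC | VR | True SE / assumed SE | Type I error |
|---|---|---|---|---|
| 0.08 | 1.0 | 1 + 1.92 − 2.00 = 0.92 | 0.96 | 4.1% |
| 0.08 | 0.96 | 1 + 1.92 − 1.92 = 1.00 | 1.00 | 5.0% |
| 0.08 | 0.8 | 1 + 1.92 − 1.60 = 1.32 | 1.15 | 8.8% |
| 0.08 | 0.5 | 1 + 1.92 − 1.00 = 1.92 | 1.39 | 15.7% |
| 0.02 | 1.0 | 1 + 0.48 − 0.50 = 0.98 | 0.99 | 4.8% |
| 0.02 | 0.8 | 1 + 0.48 − 0.40 = 1.08 | 1.04 | 5.9% |
| 0.02 | 0.5 | 1 + 0.48 − 0.25 = 1.23 | 1.11 | 7.7% |

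The break-even point is CAC = (m − 1)/m = 24/25 = 0.96, whatever the ICC. Above it the plain test is slightly conservative; below it the test rejects too often.

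**Check by simulation** (4000 runs per scenario, K = 50, m = 25). At ICC 0.08 the independent-samples t test rejected in 4.5% (CAC 1.0), 9.0% (0.8) and 15.6% (0.5) of runs, in line with the formula. A paired test on practice means, which respects the design, stayed between 4.4% and 5.4% in all six scenarios run.

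**Why the linked model should not be the default.** The article expects 66% response to the online survey. If that rate held among the 50 survey practices (an assumption), about 0.66 × 50 = 33 would have linked GP data. A pre-post test that depended on linkage would lose the other 17.

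**The case against.** The strongest reply is Table 1. Its vaccine-literacy row is the only place that pairs this outcome with analysis methods, and it lists multilevel analysis without a mean test. Table 1 also keeps two uses apart: the row for the GP and medical-assistant survey makes multilevel analysis follow linkage with patient data, while the vaccine-literacy row sets no such condition. The paragraph in Data analysis is one condensed sentence covering several surveys, and it does not tie the mean test to vaccine literacy. This stands. A reader might infer that the mean test is the only planned test of vaccine literacy; the documents do not support that.

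Second, the samples are independent at patient level, and the phrase may only be meant as the opposite of paired. That is fair, but it does not remove the dependence through practices.

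Third, a reader might infer that the error bars are simply wrong, or usually too narrow. The figures do not support that either: the direction depends on a between-wave correlation that the article does not give, and near 0.96 the plain test is about right.

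Fourth, nor does the plan leave case mix unadjusted. Multivariable regression is listed for this outcome, and sociodemographic variables are collected in both waves.

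Last, a journal article may leave random-effects detail to an analysis plan that is not shown, and the absence of that detail is not the point here. The point is that the text names a test that does not fit the sampling design and differs from the article's own table.

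**Conclusion.** The point holds as a conflict between the text and Table 1, combined with a named test that does not match the design. Neither place says which analysis answers the pre-post question on vaccine literacy.

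The numerical consequence is conditional. It arises only if the unadjusted independent-samples test carries the inference. In that case the true type I error is 4.1% to 15.7% at ICC 0.08 and 4.8% to 7.7% at ICC 0.02, for CAC from 1.0 down to 0.5. Both the ICC for literacy and the CAC are assumptions. A multilevel model with practice as a level and a suitable wave structure would deal with the problem, and Table 1 already points that way. The primary outcome is not touched. The point is worth acting on because the outcome is a named secondary one and the repair needs only wording.

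**What to change.** Bring Data analysis, Primary data, and the abstract into line with Table 1:
- State that the pre-post contrast of vaccine literacy is tested in the multilevel model of the patient survey, using all 50 practices and not conditional on linkage to the online survey.
- Specify wave as a fixed effect, with random effects for practice and for practice-by-wave. The second is needed because a random practice intercept alone implies CAC = 1 and misses the variation that drives the excess error in the table above.
- Adjust for the sociodemographic variables collected in both waves.
- Report the unadjusted comparison of means as descriptive only.
- Describe the linkage of GP online-survey data with patient data as a separate, additional multilevel analysis.

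The cost is a change of wording, with no new data. The confidence interval may become wider than the naive one: at ICC 0.08 by about 15% if CAC is 0.8, whereas at CAC 1.0 it would be about 4% narrower.

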#### Patient and public involvement

The project does not include any genuine patient and public involvement components. However, GPs are represented within the project team by the participating ASHIP. A representative of the German Association of Medical Assistants is part of the consortium as well and contributed to intervention development.

## Discussion

In this study, a complex intervention to improve vaccination rates in GP practices for the vaccinations recommended for people aged 60 years and older will be implemented and evaluated. Targeted intervention activities in the GP practices are intended to improve patients’ vaccine-related health literacy, knowledge about the respective diseases and vaccinations, and patients’ intention to get vaccinated.

The survey recruitment of patients by the GP practice team may lead to a social desirability bias. Since independent patient cohorts are surveyed pre and post intervention, no within-person comparisons can be performed. Furthermore, the dynamic developments of the COVID-19 pandemic could affect both outcomes and the feasibility of the planned study.

To the best of our knowledge, there are no comparable complex intervention studies examining vaccination uptake and vaccine literacy regarding all recommended vaccinations for persons aged 60 years and older in Germany. Therefore, the design of this intervention study can deliver results that can be used to improve preventive health care for elderly people. The mixed methods design enables a more comprehensive understanding of the complex context in which this study takes place and thus contributes to more profound knowledge on the intervention’s effectiveness.

The results will be published as a report in the final phase of the study. Depending on the results, a decision will be made by the Innovation Fund of the Federal Joint Committee, the highest decision-making body of the joint self-government of physicians, dentists, hospitals, and health insurance funds in Germany on whether the intervention will be recommended to be included into standard care in Germany. The results will be accessible to the scientific community in the form of scientific publications and conference contributions. Aggregated results of the patient surveys per GP practice can be provided to participating GPs on request.

## Data Availability

The datasets used and/or analysed during the current study available from the corresponding author on reasonable request.

## List of abbreviations

GP: General practitioner
STIKO: Standing Committee on Vaccination
ICC: Intra-cluster correlation
ASHIP: Associations of Statutory Health Insurance Physicians
SGB: V Fifth Social Security Code
HLS19: Health Literacy Population Survey Project 2019–2021
CARE: Consultation and Relational Empathy scale
MCCS: Medical Communication Competence Scale
CaPts: Information needs of cancer patients scale
ITS: Interrupted Time Series Models
EU: GDPR General Data Protection Regulation
vdek: Verband der Ersatzkassen e. V [Association of Substitute Health Funds]
